## Abstract

**Background:**

Clinical management of primary ciliary dyskinesia (PCD) respiratory disease is currently based on improving mucociliary clearance and controlling respiratory infections, through the administration of antibiotics. Treatment practices in PCD are largely extrapolated from more common chronic respiratory disorders, particularly cystic fibrosis, but no randomized controlled trials (RCT) have ever evaluated efficacy and safety of any pharmacotherapeutics used in the treatment of PCD. Maintenance therapy, with the macrolide antibiotic azithromycin, is currently widely used in chronic respiratory diseases including PCD. In addition to its antibacterial properties, azithromycin is considered to have beneficial anti-inflammatory and anti-quorum-sensing properties.

The aim of this study is to determine the efficacy of azithromycin maintenance therapy for 6 months on respiratory exacerbations in PCD. The secondary objectives are to evaluate the efficacy of azithromycin on lung function, ventilation inhomogeneity, hearing impairment, and symptoms (respiratory, sinus, ears and hearing) measured on a PCD-specific health-related quality of life instrument, and to assess the safety of azithromycin maintenance therapy in PCD.

**Methods:**

The BESTCILIA trial is a European multi-centre, double-blind, randomized, placebo-controlled, parallel group study. The intervention is tablets of azithromycin 250/500 mg according to body weight or placebo administered three times a week for 6 months. Subjects with a confirmed diagnosis of PCD, age 7–50 years, are eligible for inclusion. Chronic pulmonary infections with Gram-negative bacteria or any recent occurrence of non-tuberculous mycobacteria are exclusion criteria. The planned number of subjects to be included is 125. The trial has been approved by the Research Ethics Committees of the participating institutions.

**Discussion:**

We present a study protocol of an ongoing RCT, evaluating for the first time, the efficacy and safety of a pharmacotherapeutic treatment for patients with PCD. The RCT evaluates azithromycin maintenance therapy, a drug already commonly prescribed in other chronic respiratory disorders. Furthermore, the trial will utilize the Lung clearance index and new, PCD-specific quality of life instruments as outcome measures for PCD. Recruitment is hampered by frequent occurrence of *Pseudomonas aeruginosa* infection, exacerbations at enrolment, and the patients’ perception of disease severity and necessity of additional management and treatment during trial participation.

**Trial registration:**

EudraCT 2013-004664-58 (date of registration: 2014-04-08).

## Background

Primary ciliary dyskinesia (PCD) is a rare, congenital disease with symptom onset in the neonatal period or early childhood, with progression throughout adulthood. PCD presents with chronic rhino-sinusitis, recurrent otitis media and conductive hearing impairment, chronic productive cough and infection and inflammation of the lower respiratory tract [1, 2]. The cilia lining the respiratory epithelium are either immotile or dyskinetic and therefore cannot generate coordinated ciliary beating necessary to expel mucus [3]. The defective mucociliary clearance causes excessive mucus, bacteria and debris to accumulate in the airways, serving as a nidus for infection [4, 5]. Recurrent lower respiratory tract infections progress to chronic infection that leads to bronchiectasis. PCD causes loss of lung function and in severe cases, can result in chronic respiratory failure, with lung transplantation as the final therapeutic avenue [1, 6]. Ciliary beating is important in organ systems other than the respiratory tract such as the embryonic node, sperm flagella, female reproductive tract, and ependyma of the brain and spinal cord [3]. Patients with PCD can therefore also present with situs inversus, reduced fertility, hydrocephalus or, more rarely, complex congenital heart disease. PCD is a genetically heterogeneous disorder, which is predominantly inherited as autosomal recessive trait [1, 7]. Rough estimates of the prevalence of PCD indicate that it affects 1 in 10.000–20.000 individuals [2, 8]. PCD respiratory disease shares some similarities with cystic fibrosis (CF), in which mucociliary clearance is also impaired [9].

As with all chronic respiratory diseases, the aim of treatment for PCD is to maintain or restore normal lung function to the extent possible. The clinical management of PCD respiratory disease is focused on improving mucociliary clearance, primarily with chest physiotherapy, and controlling respiratory infections through the administration of antibiotics [1, 6, 10, 11]. No orphan drugs are available for the treatment of PCD, and the current treatment practices in PCD are extrapolated from treatment of other chronic respiratory disorders, particularly CF, and therefore based on the pathophysiology of these diseases. This strategy is questionable since PCD exhibits a different pathophysiology [1, 12]. No randomized controlled trials (RCT) have been conducted in PCD to determine the efficacy and safety of those pharmacotherapeutics currently used; and thus there are no evidence-based guidelines for pharmacotherapy of PCD patients [1, 11]. Accordingly, management strategies for PCD vary widely between and within the European countries [12]. The lack of evidence for management of PCD respiratory disease is a likely reason for the poor clinical impact on preventing decline in lung function - even when diagnosis is made at an early age [8]. Appropriate treatment of PCD will likely reduce the morbidity of PCD and prolong the life expectancy of PCD-patients.

There is anecdotal evidence of positive outcomes of long-term prophylactic antibiotic treatment in PCD [10, 11]. Over the last decade, maintenance therapy with macrolide antibiotics has been studied in a number of trials in different chronic respiratory diseases, following evidence of effectiveness of low-dose long-term therapy with erythromycin in diffuse panbronchiolitis [13]. In addition to its antibacterial properties, the macrolide antibiotic azithromycin is considered to have beneficial properties with respect to anti-inflammation and quorum sensing inhibition [13–15]. Azithromycin has a simple dosing schedule and covers a wide range of bacteria encountered in PCD respiratory infections. A Cochrane review [16] has reported a meta-analysis evaluating the efficacy and safety of azithromycin maintenance therapy in CF patients. RCTs examining azithromycin versus placebo demonstrated improvement in lung function after a treatment period of 6 months and a significant reduction in the need for additional oral antibiotics in those patients receiving azithromycin. Patients receiving azithromycin were also approximately twice as likely to be free of pulmonary exacerbation at six months [16]. Adverse events were uncommon, although more frequent gastrointestinal events were reported in one trial. Azithromycin maintenance therapy, however, has been associated with an increase in resistance to macrolides [16, 17]. Two RCTs investigating azithromycin maintenance therapy versus placebo in adult patients with non-CF bronchiectasis for 6 and 12 months, respectively, have been published [18, 19] and showed decreases in exacerbations, whereas improvement in lung function, measured by spirometry, and health-related quality of life was only found in the 12 month RCT. Azithromycin maintenance therapy was generally well-tolerated, although gastrointestinal symptoms were reported more frequently in the azithromycin group [18, 19]. Decreases in exacerbations attributable to long-term azithromycin therapy were also demonstrated in a RCT with Indigenous children with non-CF bronchiectasis or chronic suppurative lung disease [20]. Azithromycin maintenance therapy has also been shown to have efficacy in chronic obstructive pulmonary disease. However, hearing decrements were observed to be more common in the azithromycin group in a 12 month RCT in patients with chronic obstructive pulmonary disease [21]. Azithromycin maintenance therapy is currently widely used in the treatment of patients with CF [14, 22] and other chronic respiratory diseases including PCD, however there is no evidence to support its use in PCD.

### Aims

This trial will generate the first evidence-based knowledge on pharmacotherapy in PCD. The main objective is to determine the efficacy of azithromycin maintenance therapy for 6 months on respiratory system exacerbations in subjects with PCD, 7–50 years of age.

The secondary objectives of this trial are to:Determine the efficacy of azithromycin on lung function measured by spirometry, on static lung volumes and airways resistance measured by body plethysmography, and on ventilation inhomogeneity measured by nitrogen multiple breath washout (N_2_ MBW) as a new outcome measure;Assess the efficacy of azithromycin on respiratory, sinus and ear symptoms as measured by new, PCD-specific health-related quality of life outcome measure (QOL-PCD) [23];Determine the efficacy of azithromycin on hearing impairment;Determine the efficacy of azithromycin on sputum microbiology and inflammatory markers;Assess the safety of azithromycin maintenance therapy in PCD.

This study tests the hypothesis that maintenance therapy with azithromycin provides significant improvement in PCD respiratory disease compared to placebo, by reducing respiratory system exacerbations and by improving lung function, ventilation inhomogeneity, health-related quality of life and hearing impairment. Maintenance therapy with azithromycin is expected to be safe with no serious adverse events compared to placebo.

## Methods/Design

### Study design

This study is a multi-centre, parallel group, double-blind, randomized, placebo-controlled trial with azithromycin maintenance therapy in subjects with PCD (Fig. 1).

**Fig. 1 Fig1:**
[figure not shown]
Trial flow chart

### Recruitment

Eligible patients are identified from six European PCD outpatient clinics (see Table 1). Patients and their parents are approached and informed consent obtained.

**Table 1 Tab1:** Eligible patients and recruitment plans

Trial sites:	Estimated no. of eligible patients:	Recruitment strategies:
Copenhagen University Hospital, Rigshospitalet, Denmark	30	- Patients attending the outpatient clinic.
		- Information at PCD patient event.
University Children's Hospital Muenster, Germany	30	- Patients attending the outpatient clinic.
		- Advertisement via the national PCD patient organization.
		- Information through the German Pediatric Pulmonology Society.
Inselspital Bern, Switzerland	10	- Patients attending the outpatient clinic.
		- Information to patients in the national PCD registry.
VU University Medical Center Amsterdam, Netherlands	20	- Patients attending the outpatient clinic.
		- Advertisement via the national PCD patient organization.
		- Contacting pediatric pulmonologists caring for PCD patients at other academic centers.
University Hospital Southampton, United Kingdom	10	- Patients attending the outpatient clinic.
		- Advertisement via the national PCD patient organization.
Royal Brompton Hospital, United Kingdom	40	- Patients attending the outpatient clinic.
		- Advertisement via the national PCD patient organization.
Total	140	

### Intervention

The intervention is oral tablets of azithromycin or identical tablets of placebo administered three times a week (Monday-Wednesday-Friday) for 6 months. The dose of azithromycin is 250 mg for participants with a body weight below 40 kg at screening and 500 mg for participants weighting 40 kg or above, corresponding to a weekly dose of 750 mg or 1500 mg azithromycin, respectively.

Systemic or inhaled antibiotic treatment, besides the potential azithromycin maintenance therapy during the trial, is only allowed if needed during clinical exacerbations and in the case of new infection with *Pseudomonas aeruginosa*, *Achromobacter xylosoxidans* or *Burkholderia complex*. Treatment of respiratory system exacerbations, if culture and antibiotic susceptibility is not yet known, will be 14 days of oral amoxicillin with clavulanic acid as first-line treatment and clarithromycin as second choice. More severe exacerbations will be treated according to local guidelines. Treatment of first time or intermittent colonization with *Pseudomonas aeruginosa* will be inhalation of colistin in combination with oral ciprofloxacin or inhalation of Tobramycin for 3-4 weeks. In case of treatment failure, early relapse or signs of development of chronic *Pseudomonas aeruginosa* infection, antibiotic treatment will be intensified to last for 3 months. Treatment with the trial medication will continue throughout the trial simultaneously with any antibiotics prescribed for exacerbations or infection with *Pseudomonas aeruginosa*. Any other pre-trial medication will continue unchanged, and any other new prescriptions, which are considered necessary for the participant’s welfare, may be given.

### Randomization, allocation and blinding

Participants will be randomly assigned to one of the two treatment arms in a 1:1 ratio with stratification according to age (7–12 years; 13–21 years; and 22–50 years). The allocation sequence is a permuted-block randomization and has been generated by an external consultancy (Datamanagement, Public Health and Quality Improvement, Central Denmark Region, Aarhus, Denmark). Participants will be assigned to the intervention by delegated study staff via an online randomization module in an electronic Case Report Form (‘TrialPartner’, Datamanagement, Denmark). The allocation is concealed to the investigative staff and sponsor throughout the study, and unblinding will only occur in the event of a Suspected Unexpected Serious Adverse Reaction or if otherwise required for patient safety.

A hospital pharmacy (Apotheek Haagse Ziekenhuizen, The Hague, The Netherlands) is responsible for preparation of the trial medication. Azithromycin tablets bought from a pharmaceutical company are repackaged and identical placebo tablets are specifically manufactured by the hospital pharmacy. Blinded labelling and packaging of the trial medication in identical blister packages in carton boxes is performed centrally at the hospital pharmacy according to Good Manufacturing Practice. Adherence to the trial treatment will be assessed by participant/parent report and count of returned trial medications.

### Data collection

Participants will be screened for eligibility in a stable state after having given informed consent to participation. At screening, demographic information (age, gender, ethnicity) will be recorded and inclusion- and exclusion criteria review will be performed, including data on medical history, current symptoms and concomitant medication, physical examination, pregnancy test, electrocardiogram, spirometry, and sputum microbiology. The QOL-PCD [23] will be completed by participants both one week prior to screening and again at the screening visit to obtain baseline values. Screening will be followed by a run-in period of one month to ensure that participants have stable lung function (defined as maximal decrease in FEV_1_% predicted of 10 percentage points from the screening visit to the randomization visit) and that prohibited medications are washed out at randomization. Participants will be withdrawn prior to randomization if they have an exacerbation or receive systemic or inhaled antibiotics at the screening or randomization visit, or if they have received antibiotics for more than 2 weeks during the run-in period. Participants will be reviewed every two months during the 6 months treatment period. Participants will be asked to contact the trial site at the onset of an exacerbation, if possible, and exacerbations will be reviewed at extra visits or by telephone contact. Withdrawal of participants during the trial will occur if the participants fulfil any of the exclusion criteria or due to safety reasons. A QOL-PCD will be completed by the participants, as a follow-up assessment 2 months after the end of the treatment period.

All data will be recorded in an electronic case report form. The primary and secondary outcome measures (see below) are collected at the specified time points. All adverse events occurring from the first administration of the trial medication to the end of the last trial visit will be recorded and monitored (Table 2).

**Table 2 Tab2:** Time and events schedule

	Screening	Treatment period				Follow-up
	Visit *0 months*	Visit *1 month (+2 weeks)*	Visit *3 months (+/- 1 week)*	Visit *5 months (+/- 1 week)*	Visit *7 months (+/- 1 week)*	*9 months*
Informed consent	X					
Demographics	X					
Inclusion/Exclusion criteria review	X					
INTERVENTION:						
Randomization		X				
Azithromycin/Placebo						
Adherence			X	X	X	
ASSESSMENTS:						
QOL-PCD	X	X	X	X	X	X
Patient interview	X	X	X	X	X	
Concomitant medication	X	X	X	X	X	
Weekly patient diary		X	X	X	X	
Physical examination & vital signs	X	X	X	X	X	
Pregnancy test	X	X	X	X	X	
Electrocardiogram	X					
Spirometry	X	X	X	X	X	
Body plethysmography		X	X	X	X	
N_2_ MBW		X	X	X	X	
Audiometry & tympanometry		X			X	
Sputum microbiology & antibiotic susceptibility	X	X	X	X	X	
Inflammatory markers (sputum & blood)		X			X	
Blood samples (bone marrow, liver & kidney)		X			X	

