#### Health-related quality of life

Newly developed, PCD-specific health-related quality of life questionnaires (QOL-PCD) will be used to assess patient-reported outcomes [23]. The QOL-PCD has age-appropriate versions available for children 6–12 years, adolescents 13–17 years, adults, and a parent proxy. The following domains on the QOL-PCD will be used as outcome measures: Respiratory Symptoms, Sinus Symptoms, and Ears and Hearing. The QOL-PCD is available in the primary languages of the participating countries (English, Danish, Dutch, German and Swiss German), and an electronic speaking questionnaire is available for the youngest age group. The QOL-PCD will be completed at all visits, at extra contacts with trial sites attributable to exacerbations, and will be administered prior to any other study procedures to reduce bias.

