The RCT is currently ongoing and participants have been enrolled at all trial sites. Recruitment is hampered by our choice to exclude PCD patients with chronic *Pseudomonas aeruginosa* infection and patients receiving systemic or inhaled maintenance antibiotics to limit the impact of concomitant antibiotic therapy. *Pseudomonas aeruginosa* infection has proved to be more common in PCD than previously anticipated [5]. PCD patients without chronic infection are not used to this frequent and time consuming follow-up, and, in contrast to CF patients, PCD patients are in general less well organised in patient organizations, which seem to influence their interest in sacrificing time and burden in research (see Table 3 for reasons for recruitment issues). Scarce knowledge on prognosis and clinical sub-phenotypes in PCD among both physicians and patients probably affects the perception of disease severity. PCD patients and physicians may have different views on the appropriate extent of management and treatment, which is important to take into consideration when designing future trials in PCD. Another limiting factor for inclusion in this trial is the requirement of clinical stability at enrolment, which is challenging in PCD characterized by frequent respiratory exacerbations and a chronic, but somewhat fluctuating degree of respiratory symptoms. Initially, the protocol did not allow any change in medication from the screening visit and throughout the run-in period lasting up to 1½ month. However, we have been forced to allow some oral antibiotics during this period. The fluctuating nature of the PCD disease and the considerable number of patients being on various more or less permanent antibiotic regimens should be carefully considered and weighed against the aims of including only stable and comparable patients, when designing clinical trials in the future.

**Table 3 Tab3:** Reasons for recruitment issues

Major reasons for refusal of participation:	
Due to patients’ views:	
	- Long travel distance to trial site.
	- Time consuming (e.g. not possible to take time off work).
	- Fear of adverse reactions.
	- Treatment burden.
	- Not perceiving themselves/their child as being ill and therefore finding medical maintenance therapy unnecessary.
	- Not seeing any personal gain in taking part in the research.
	- Already on maintenance antibiotics and not willing to discontinue this treatment.
	- Fear of blood sampling.
Due to eligibility criteria in study protocol:	

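### The stated QOL-PCD baseline comes only from scores taken about 4 to 7 weeks before randomisation and leaves out the score already collected at randomisation; the comparison is not biased, but precision can be lost

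*Protocol article*

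**What the plan says.** Under Data collection, the protocol article states that the QOL-PCD "will be completed by participants both one week prior to screening and again at the screening visit to obtain baseline values". It continues: "Screening will be followed by a run-in period of one month to ensure that participants have stable lung function" and "that prohibited medications are washed out at randomization". Table 2 places the randomisation visit at month 1 with a window of up to two further weeks, and the Discussion describes a period "throughout the run-in period lasting up to 1½ month".

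The run-in is not free of treatment. Participants are withdrawn before randomisation if they have an exacerbation or are on systemic or inhaled antibiotics at either visit, "or if they have received antibiotics for more than 2 weeks during the run-in period". The Discussion adds that "we have been forced to allow some oral antibiotics during this period".

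The section on health-related quality of life says "The QOL-PCD will be completed at all visits, at extra contacts with trial sites attributable to exacerbations", and Table 2 marks a QOL-PCD at the randomisation visit. No section says that this score serves as baseline.

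Three QOL-PCD domains are secondary outcomes: respiratory symptoms, sinus symptoms, and ears and hearing. The Statistical analysis section models continuous secondary outcomes with a linear mixed model. It does not say how baseline enters.

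**The concern.** The article says which completions supply the QOL-PCD baseline, and they are the two furthest from treatment. Symptoms can change between them and randomisation for reasons unrelated to trial medication: wash-out of prohibited medication, a short antibiotic course between visits, or the fluctuation in symptoms that the Discussion itself describes.

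Two things follow if the early scores alone are used. Any reported change from baseline contains run-in change as well as change on treatment. An older baseline may also predict the follow-up score less well, so that adjusting for it removes less variance. The Discussion presents evaluation of new outcome measures as a secondary focus of the trial, so the baseline of this instrument should be well chosen.

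**Working it through.** **1. Age of the stated baseline.** One month is 365.25 / 12 / 7 = 4.35 weeks. Randomisation falls 0 to 2 weeks after that point (Table 2).

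- Screening score to randomisation: 4.35 to 6.35 weeks, or 1.00 to 1.46 months. This reproduces the one month in Data collection and the month and a half in the Discussion.
- Score from one week before screening: 5.35 to 7.35 weeks, or 1.23 to 1.69 months.
- Score at the randomisation visit: about 0 weeks, taking first dose to be at randomisation, since no separate day is given.

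**2. Direction of any error between arms.** The two early scores and the randomisation score are all obtained before allocation or at the visit where it happens, before treatment. Their expected values are equal in the two arms, so the choice among them affects variance and not the expected treatment contrast.

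**3. Precision.** The article gives no power and no correlations for the QOL-PCD, so everything here is assumed: equal variance at all times; a single early score correlating r = 0.60 with follow-up; the two early scores correlating ρ = 0.70 to 0.80 with each other; the randomisation score correlating 0.65 to 0.70 with follow-up. The two early scores are taken to be averaged, which the article does not state.

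The correlation of the early mean with follow-up is r / √((1 + ρ)/2):

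- ρ = 0.70: 0.60 / √0.85 = 0.651
- ρ = 0.80: 0.60 / √0.90 = 0.632

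The residual variance after adjustment for baseline is 1 − correlation²:

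- early mean: 1 − 0.36/0.85 = 0.576 (ρ = 0.70); 1 − 0.36/0.90 = 0.600 (ρ = 0.80)
- randomisation score: 1 − 0.65² = 0.5775; 1 − 0.70² = 0.510

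The ratio of early to randomisation residual variance is the relative effective sample size:

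| | randomisation r = 0.65 | randomisation r = 0.70 |
|---|---|---|
| ρ = 0.70 | 0.576/0.5775 = 1.00 | 0.576/0.510 = 1.13 |
| ρ = 0.80 | 0.600/0.5775 = 1.04 | 0.600/0.510 = 1.18 |

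The gain is 0 to 13% at ρ = 0.70 and 4 to 18% at ρ = 0.80.

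**4. Replacing or including.** If simple change scores were used, the variance of change from the early mean would be 1 + (1 + ρ)/2 − 2(0.60), that is 0.65 or 0.70. From the randomisation score it would be 2(1 − 0.65) = 0.70 or 2(1 − 0.70) = 0.60. The ratios run from 0.65/0.70 = 0.93 to 0.70/0.60 = 1.17, so a bare swap could lose a little. If the randomisation score is a covariate and the early mean is added as a second one, the residual variance cannot exceed that with either alone, apart from one extra parameter.

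**The case against.** The strongest reply is that the quoted sentence sits in a paragraph on data collection and does not fix the analysis. A repeated-measures model can take the randomisation score as a pre-treatment observation, and the full protocol or analysis plan may settle this. That stands: an analysis error is not shown. What remains is that the article assigns the word baseline to two completions and omits the third.

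Several stronger readings are tempting and are not supported:

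- **Bias in the treatment effect.** A reader might infer that run-in antibiotics distort the comparison. They cannot do so through the choice of baseline, because all these scores precede allocation. Within-arm change is also not a stated objective.
- **A gain of 11 to 25%.** Comparing one early score with one randomisation score gives 0.64/0.5775 = 1.11 and 0.64/0.51 = 1.25. The plan has two early completions, and averaging them recovers part of that gain.
- **QOL-PCD alone starts before the run-in.** Spirometry and sputum microbiology also start at screening. Because QOL-PCD is completed at randomisation, it can still be aligned with the measures that start there.
- **A questionnaire before consent.** Data collection puts consent before screening, and Table 2 has no column for a pre-screening completion. The table does not show that consent comes later than the first questionnaire.

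A randomisation-only baseline also has weaknesses. Participants are selected for stability at that visit too, and one score is less reliable than the mean of two. This stands, and it is why the randomisation score should be added and not simply substituted.

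**Conclusion.** The point holds as a minor one. The stated QOL-PCD baseline is about 4 to 7 weeks old at randomisation, precedes the wash-out and any run-in antibiotics, and leaves out a later score that is already collected. It does not bias the azithromycin-placebo comparison. It can lose precision on three secondary domains, and it puts run-in change into any reported change from baseline.

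The precision loss is nil to modest: about 0 to 13% of effective sample size if the two early scores correlate 0.70, and up to 18% if they correlate 0.80. These figures rest wholly on assumed correlations, on averaging of the early scores, and on adjustment for baseline, none of which the article states. The timing rests on the article's own schedule and is firm.

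**What to change.** In Data collection, define the QOL-PCD baseline so that it includes the randomisation-visit score. Either of two forms will do: the mean of the pre-dose scores including randomisation, or the randomisation score with the mean of the two earlier scores as a further covariate. The article's own FEV1 reference for exacerbations, an average over screening and randomisation, is a precedent for the first form. Keep the two earlier completions for test-retest reliability as well.

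The questionnaire is already completed at randomisation, so there is no added burden on participants and no change to sample size. The cost is a small change to the analysis wording, best made before unblinding.
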